### Blinding

Due to the nature of the intervention, blinding will not be feasible at the level of HWs. Measures will be taken to minimise ascertainment bias by training the research team in standardised data collection methods. The investigators will monitor this.

### Outcome assessment

Outcomes will be measured at both the PHC and participant levels and have been outlined in Table 3.

**Table 3 Tab3:** Study outcome according to various phases and data sources

Outcome measures	Respondents	Data collection type
*Objective 1*		
* 1. Themes and sub-themes*	DMHP stakeholders, HWs, community members	Qualitative interviews
* 2. Pre and post training scores*	HWs	Study questionnaire
* 3. User validity testing*	DMHP stakeholders, HWs	Observation checklist
*Objective 2*		
* 1. Detection rates of depression*	HWs, adults	Study monitoring forms; application data
* 2. Treatment completion rates*	HWs, adults	Study monitoring forms; application data
* 3. Referral rates*	HWs, adults	Study monitoring forms; application data
* 4. HRQoL scores*	Adults	Study questionnaire
*Objective 3*		
* 1. Acceptability*	HWs	AIM; Qualitative interviews
* 2. Feasibility*	HWs	AIM; Qualitative interviews
* 3. Fidelity*	HWs	AIM; Qualitative interviews, Study monitoring forms
* 4. Theme and sub-themes*	HWs	Qualitative interviews
*Objective 4*		
* 1. Incremental cost effectiveness ratio*	HWs, adults, DMHP stakeholders	Study questionnaire, administrative data, project reports

Acceptability and feasibility: This will be assessed using both quantitative and qualitative methods in the intervention arm. (1) Feasibility: Recruitment and attrition rates will be estimated, and intervention fidelity will be monitored using standard study forms, with any protocol deviations documented. (2) Acceptability: HWs’ acceptance of the intervention will be measured using the Acceptability of Intervention Measure (AIM) instrument. Developed by implementation scientists, the AIM instrument has displayed good psychometric properties [42]. At the end of the trial, FGDs will be conducted with the HWs to understand their perceptions and experiences of using the application.

Cost-effectiveness of the intervention: Cost-effectiveness analysis will be conducted from a societal perspective by listing, measuring, and valuing all costs involved in delivering the intervention. An ingredients approach will be used to collect information on quantities and prices of all resources across three categories: (a) Costs of providing the intervention—includes direct and indirect costs training, application development, consumables, time, human resource, outpatient visits, and counselling. (b) Costs of accessing the intervention—includes patient resources such as travel costs to the PHC and opportunity costs. (c) Overhead costs—includes personnel costs based on salaries and time spent on the intervention as well as utilities. Cost valuation will ensure transferability of cost over time, with the Consumer Price Index used to adjust for inflation. A 3% discount rate, as recommended by the WHO, will be applied.

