**Methods:**

Formative phase will involve qualitative interviews, literature review aimed at co-developing a mobile application with the district mental health program. This will be followed by a cRCT. The trial will be conducted in eight PHCs, located in Tumkur district, Karnataka, and Wardha district, Maharashtra. Randomisation will be done at the PHC level. We plan to enrol non-specialist HWs working in these PHCs and a sample of 2400 adults who are availing the PHC services. Intervention PHC will receive training for HWs and a mobile application. Control PHCs will follow usual care. Both the groups will be encouraged to identify, manage, and follow-up people with mild depression. Study tools include PHQ-2, PHQ-9, acceptability of intervention measure, and Eq. 5D5L instrument. Change in the detection rates of depression between intervention and control arms will be the primary outcome. Cost effectiveness analysis will be done.

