## Background

Globally 280 million people were suffering from depressive disorders, and it accounted for the largest proportion of mental disorder Disability Adjusted Life Years (DALYs) of 37.3% in 2019 [1]. In India, depression affected over 5% of the adult population [2]. Despite availability of effective interventions, the vast majority of people with depression do not receive any care [3, 4]. Untreated depression is a leading cause of disability and suicide [5]. Compared to general population, people with depression have a 40–60% higher chance of premature mortality [6–8]. Yet, detection rates of depression in the primary care settings is extremely low and reports suggest that > 90% of the cases go undetected in low- and middle-income countries (LMICs) leading to a huge treatment gap [9–10].

India provides health services including mental healthcare through a three-tier public health system [11]. Through the National Mental Health Program (NMHP), India envisages providing universal access to mental healthcare [12]. The District Mental Health Programme (DMHP) under NMHP focuses on delivering mental healthcare in a decentralized manner. In many states, DMHP has launched specific programs to integrate mental healthcare into public health facilities [13]. However, the success of these programs are limited to district level [14]. 

One of the barriers to integrating mental healthcare into primary care includes shortage of human resources [3, 6]. India faces hurdles in delivering mental healthcare due to a shortage and unequal distribution of trained mental health professionals between urban and rural areas [3]. Low mental health literacy, persisting stigma and discrimination in rural India, further exacerbates this issue [15]. Therefore, task-sharing, a process of training non-specialist health workers (HWs) to contribute to detecting, diagnosing, and treating various mental disorders, is a promising strategy [16]. Evidence shows that interventions such as training HWs, screening, feedback, and standard guidelines led to improved detection of depression at the primary level [17]. Increasingly, such task sharing strategies targeting primary-level HWs are being emphasized by the DMHP [14]. 

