**Fig. 2 Fig2:**
[figure not shown]
Consort flow diagram

Phase I: In this, baseline data collection using outpatient records in all study PHCs will be carried out to determine the PHC footfall, number of adults diagnosed, managed, or referred for mental health conditions over the past six months.

Phase II: PHCs will be randomised and allocated into the intervention arm (*n* = 4) and the control arm (*n* = 4). Subsequently, intervention package will be delivered to HWs in the intervention PHCs. HWs at the control PHCs will receive a one-day sensitisation session on mental health conditions, including brief psychoeducational counselling on depression.

Phase III: Screening, assessment, psychological counselling of adult participants by HWs, and referrals will take place during this phase. In both intervention and control PHCs, adults attending the study PHCs will be enrolled consecutively ss per the eligibility criteria. They will be allotted to each HW depending on the availability of HW in the PHCs for screening, assessment, and management of depression.

Phase IV: In both arms, participants identified with mild depression will receive psychological counselling from HWs and will be followed up as outlined in the pilot phase. Each follow-up counselling session will last 10 min per participant. PRS will give telephonic reminders to participants to reduce dropouts. Screening, assessment, and management of mild depression will be done using application in intervention PHCs and through usual care in control PHCs by the HW.

Validation by PRS: At the time of baseline assessment, the PRS will validate all participants identified with mild depression by HWs. Along with this, PRS will also randomly conduct a validation check PHQ 9 scores in participants identified as normal by HWs. To document changes in PHQ-9 scores, the PRS will administer the PHQ-9 to participants at all follow-up visits. PRS will do a health-related quality of life (HRQoL) assessment at baseline and the last follow-up.

Referral: Participants with PHQ-9 scores ≥ 10 or having suicidal ideation will be referred to the DMHP psychiatrist at the sub-district hospital. The PRS will contact participants telephonically to ensure they receive appropriate care. Throughout the study, the research team will provide weekly supportive supervision to all HWs in both arms to provide feedback and address any issues they may face.

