### Sample size

The sample size was calculated by considering a 5% detection rate of depression at primary care level [9, 10] and assuming a difference in detection rate by 20% between the intervention and control arm. Assuming an equal cluster size of 300, we will require 4 PHCs in each arm. Considering 20% attrition rate, intra-class correlation (ICC) as 0.1 [43], with 80% power, 5% alpha error for two-sided test, the minimum sample size required is 1200 adults per arm. Assuming the usual recovery rate for depression at the primary level to be 54% and an expected difference of 20% in the recovery rates between intervention and control arms, with 80% power, 5% alpha error for two-sided test, the required estimated sample size is 89 patients in each arm. Therefore, a minimum of 1200 participants per arm will be sufficient.

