### Data collection methods

Qualitative interviews will be conducted using IDI and FGD guides, prepared by the research team. Pre-training and post-training knowledge of HWs will be assessed using mhGAP knowledge questionnaire [44]. 

Screening and assessment of participants will be done using the PHQ-2 and PHQ-9. PHQ-2 has been recommended as a pre-screen prior to administering PHQ-9 items [45]. A score of ≥ 3 requires further assessment with PHQ-9 to determine severity of depression. The PHQ-9, designed for primary care settings, consists of 9 items which measure the frequency of depressive symptoms over the past fortnight. A multicentric Indian study reported PHQ-9 reliable for screening depression by HWs [46]. Table 5 provides the operational definitions of our study.Acceptability and feasibility of the intervention will be assessed using AIM instrument [47]. 

The HRQoL will be measured at baseline and endline by the PRS using EUROQUAL instrument (EQ-5D-5 L), the norms of which are available for the Indian population [48]. 

Detailed costing of every single ingredient will be gathered for doing cost-effectiveness analysis.

**Table 5 Tab5:** Operational definition for PHQ-9 used in the study

Operational definition	PHQ-9 score
*1. Normal*	< 5
*2. Mild depression*	5–9
*3. Moderate depression*	≥ 10
*4. Severe depression*	≥ 15
*5. Recovery*	< 5

The socio-demographic details from participants will be used to generate a unique identification number (UID).

In the intervention arm, screening, assessment, and counselling of participants by HWs, validation by the PRS and follow-up data will be captured in the mobile application. This data will get stored in the application backend which can be downloaded in Microsoft Excel format. In the control arm, screening, assessment, follow-up, and validation data will be captured using a case record form (CRF). This along with the HWs knowledge scores, EQ-5D-5 L scores, AIM scores, and costing data will be collected using Epicollect5 with appropriate quality checks to minimise errors. Respective site PIs will constantly monitor all the data captured through the application and by Epicollect5.

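### The primary detection rate has no stated numerator, denominator or link to the PRS validation, and its 5% planning value appears to be a share of true cases applied to all enrolled adults

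*Protocol article*

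**What the plan says.** The Abstract names the primary outcome: "Change in the detection rates of depression between intervention and control arms will be the primary outcome". Table 3 (Outcome assessment) lists it as "1. Detection rates of depression", with health workers (HWs) and adults as respondents and study monitoring forms and application data as sources. No section gives a numerator or a denominator.

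The Implementation section, under validation, says that at baseline "the PRS will validate all participants identified with mild depression by HWs", and that "PRS will also randomly conduct a validation check PHQ 9 scores in participants identified as normal by HWs". The fraction of normals to be checked is not given. Validation of people whom HWs place at PHQ-9 of 10 or more is not described. Under Data collection methods, the application holds the validation data in the intervention arm. For the other arm: "In the control arm, screening, assessment, follow-up, and validation data will be captured using a case record form (CRF"). Statistical methods compares detection rates by GEE without saying which status is analysed.

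On the planning value, the Background cites references 9 and 10 for the statement that "reports suggest that > 90% of the cases go undetected in low- and middle-income countries (LMICs"). The Sample size section cites the same two references when "considering a 5% detection rate of depression at primary care level", adds a 20% difference, and arrives at 4 PHCs of 300 adults per arm. Those adults are consecutive eligible attenders, not known cases.

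**The concern.** A detection rate can mean two things: the share of people with depression whom the HW finds, or the share of all adults seen whom the HW labels as depressed. The first needs a count of true cases. The second can rise without any more cases being found. The Background uses the first meaning, while the sample size and enrolment imply the second.

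Two things are at stake. First, the 5% and 25% may sit on the wrong denominator, so the stated power may not belong to the outcome that is analysed. Second, HWs are not blinded, and only intervention HWs have the three-day training and the application. If their raw labels are the outcome, a greater readiness to label would count in the intervention's favour, and a positive result could not separate better detection from more labelling.

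**Working it through.** **Inputs from the article.** 5% against 25%; 4 PHCs per arm; 300 adults per PHC; ICC 0.1; two-sided 5%; 80% power; 20% attrition. The 20% difference must be absolute: 5% against 6% would need 8158 per arm before clustering.

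**Input not in the article.** The prevalence of PHQ-9 of 5 or more among PHC attenders. I assume 5% to 20% and show the range.

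**The plan's own figure.** The two-proportion formula gives 49 per arm. The design effect is 1 + (300 - 1) x 0.1 = 30.9. So 49 x 30.9 = about 1514 per arm before attrition and 1514/0.8 = about 1893 after, not 1200. That mismatch is a separate matter and does not decide this point.

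**Method for power.** Effective n per arm = 4m/[1 + (m - 1) x 0.1], where m is the number per PHC in the denominator. SE = sqrt{[p0(1 - p0) + p1(1 - p1)]/effective n}. Power comes from a noncentral t with noncentrality (p1 - p0)/SE and 8 - 2 = 6 df.

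**Reading A: 5% and 25% are rates over all adults.** m = 300, effective n = 1200/30.9 = 38.8, SE = sqrt(0.235/38.8) = 0.078, noncentrality 0.20/0.078 = 2.57. Power is 58%.

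**Reading B: 5% and 25% are shares of true cases, with true cases as denominator.** m = 300 x prevalence.

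| Assumed prevalence | Cases per PHC | Design effect | Effective n per arm | Power |
|---|---|---|---|---|
| 5% | 15 | 2.4 | 25.0 | 41% |
| 10% | 30 | 3.9 | 30.8 | 48% |
| 20% | 60 | 6.9 | 34.8 | 53% |

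**Reading C: 5% and 25% are shares of true cases, but the outcome is counted over all adults.** Rate over all adults = sensitivity x prevalence + (1 - specificity) x (1 - prevalence). With no false positives the second term is zero.

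| Assumed prevalence | Control | Intervention | Difference | Power |
|---|---|---|---|---|
| 5% | 0.05 x 0.05 = 0.25% | 0.25 x 0.05 = 1.25% | 1 point | 7% |
| 20% | 0.05 x 0.20 = 1% | 0.25 x 0.20 = 5% | 4 points | 14% |

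The normal-theory variance is rough at rates this low, so the power in reading C indicates order of size only.

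**What a 25% rate over all adults requires.** Without false positives, sensitivity x prevalence = 0.25, so prevalence must be at least 25%.

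**How labelling alone could produce the planned effect.** With sensitivity unchanged, a 20-point rise over all adults needs the false-positive rate to rise by 0.20/(1 - prevalence). That is 21 points at 5% prevalence and 25 points at 20%. This matters only if raw labels are analysed.

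**The case against.** The strongest reply is that the validation exists and reaches the data. The PRS checks every participant whom HWs identify with mild depression and a random set of those called normal. The application and the control-arm CRF, from which the outcome appears to be drawn, both hold validation data. A condensed article may leave the exact counting rule to a fuller document. This stands as far as it goes. A reader might infer that the labels go unverified, or that validation has no role in the outcome; the article supports neither. What it lacks is a statement of which status is counted.

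A reader might also set the Background's figure of over 5% of Indian adults against a 25% detection rate and infer that most labels must be false. That does not follow. The figure is a lower bound for depression in the general population, whereas the trial counts PHQ-9 of 5 or more among people attending a PHC, whose prevalence is not given.

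Nor does application capture in one arm and a CRF in the other show biased capture. The control data are also entered in Epicollect5 with quality checks, and the PRS enrols participants in both arms.

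On power, most of the shortfall from 80% under reading B comes from having eight clusters at ICC 0.1. Reading A already gives only 58%, so the change of denominator accounts for about 5 to 17 points.

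Finally, the cited references are not visible and might contain more than one rate; missing over 90% of cases is not the same as detecting exactly 5%. The mismatch is therefore an inference from shared citations. It is a strong one, and the sample size is fixed in this article, so a later analysis plan cannot repair it.

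**Conclusion.** The point holds in this form: the sole stated primary outcome has no stated numerator, denominator or link to the PRS validation, and its planning value appears to be a share of true cases applied to all enrolled adults. Depending on the reading, power is about 58% (all adults at face value), 41-53% (true cases as denominator) or 7-14% (shares of cases counted over all adults). These figures rest on ICC 0.1, 6 df, 300 adults per PHC and an assumed prevalence of 5% to 20%. That over-labelling would count as success is conditional on raw HW labels being analysed, which the article neither states nor excludes. This should be settled before the outcome is analysed, because the answer changes both what a positive result means and what the trial can detect.

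**What to change.** 1. Define the primary outcome as HW-identified and PRS-confirmed on PHQ-9, divided by all enrolled adults. The PRS check should cover every HW-identified positive, including those at PHQ-9 of 10 or more, and be applied identically in both arms.
2. Fix the sampling fraction f for the planned random check of HW normals and state who is in its frame, including those screened out on PHQ-2. Use it for a key secondary, the case-based detection rate: confirmed detections/(confirmed detections + cases found among sampled normals/f).
3. Restate the 5% and 25%, and the resulting power, on the chosen denominator, with the assumed prevalence given.

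The cost is mainly wording, a fixed fraction, and a modest number of extra PRS PHQ-9 checks for HW-identified moderate or severe cases; validation of mild cases is already planned. The confirmed rate will be lower than the raw rate, and the stated power will look less favourable. The article does not say that the PRS is blinded to arm, so confirmation reduces ascertainment bias but does not remove it.

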### Participant timeline

The participant timeline has been presented in Table 4.

**Table 4 Tab4:** Participant timeline

	Year 1				Year 2				Year 3			
Project activities	1	2	3	4	1	2	3	4	1	2	3	4
Administrative permissions	X											
Development of mobile application		X	X	X								
Development of training modules			X	X								
Pre-trial pilot phase												
Pilot study				X	X							
Trial phase												
Selection of PHCs					X							
Recruitment of HWs					X							
Baseline data collection					X	X						
Randomisation						X						
Delivery of intervention						X	X	X				
Recruitment of adult participants							X					
Screening and counselling by HWs							X	X	X			
Follow-ups and outcome assessments							X	X	X	X		
Post-trail phase												
Measurement of costs							X	X	X	X		
Acceptability & feasibility measures										X		
Analysis, & report preparation									X	X	X	X
Project conclusion												X

### Sample size

The sample size was calculated by considering a 5% detection rate of depression at primary care level [9, 10] and assuming a difference in detection rate by 20% between the intervention and control arm. Assuming an equal cluster size of 300, we will require 4 PHCs in each arm. Considering 20% attrition rate, intra-class correlation (ICC) as 0.1 [43], with 80% power, 5% alpha error for two-sided test, the minimum sample size required is 1200 adults per arm. Assuming the usual recovery rate for depression at the primary level to be 54% and an expected difference of 20% in the recovery rates between intervention and control arms, with 80% power, 5% alpha error for two-sided test, the required estimated sample size is 89 patients in each arm. Therefore, a minimum of 1200 participants per arm will be sufficient.

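### The recovery sample size of 89 per arm leaves out clustering and attrition and is compared with 1200 screened adults, so 80% power for recovery is not supported

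*Protocol article*

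**What the plan says.** The Sample size section of the protocol article makes two calculations.

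- **Detection.** It starts by "considering a 5% detection rate of depression at primary care level" and "assuming a difference in detection rate by 20% between the intervention and control arm". It adds ICC 0.1 and 20% attrition, and arrives at 1200 adults per arm: "Assuming an equal cluster size of 300, we will require 4 PHCs in each arm".
- **Recovery.** "Assuming the usual recovery rate for depression at the primary level to be 54" per cent and "an expected difference of 20% in the recovery rates between intervention and control arms", it states that "with 80% power, 5% alpha error for two-sided test, the required estimated sample size is 89 patients in each arm". No ICC and no attrition are listed here. The section then declares 1200 per arm enough: "the required estimated sample size is 89 patients in each arm. Therefore, a minimum of 1200 participants per arm will be sufficient".

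Under Implementation, Phase IV, "participants identified with mild depression will receive psychological counselling from HWs and will be followed up". Referral sends participants with PHQ-9 of 10 or more to the psychiatrist. Table 5 defines recovery as PHQ-9 below 5. Statistical methods compares recovery between arms with a GEE that has an exchangeable correlation structure, to allow for clustering. The Abstract names detection as the primary outcome.

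**The concern.** Two things do not fit. First, the same section applies a cluster ICC and attrition to detection and neither to recovery, yet recovery will be analysed with cluster adjustment. Second, the closing sentence compares a requirement in depressed patients with a supply of screened adults and never converts one into the other.

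The second primary objective covers management as well as detection, and recovery is the only management measure with a power statement. If the 80% is not real, a null recovery result could be read as good evidence of no benefit when the comparison had limited power to show one.

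**Working it through.** **Inputs (Sample size unless noted).** Recovery 54% v 74%; two-sided 5%; 80% power; control detection 5%; detection difference 20%; 4 PHCs per arm; 1200 adults per arm. ICC 0.1 and attrition 20% are given for detection only. Follow-up of mild cases only is from Implementation, Phase IV.

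**1. Reproduce 89.** Mean proportion (0.54 + 0.74)/2 = 0.64.

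n = [1.96 √(2 × 0.64 × 0.36) + 0.8416 √(0.54 × 0.46 + 0.74 × 0.26)]² / 0.20² = [1.3305 + 0.5588]² / 0.04 = 89.2.

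The plan's figure therefore has design effect 1 and no attrition. Attrition alone would make it 89/0.8 = 111.25, so 112.

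**2. Convert screened adults to cases.**

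- Control: 0.05 × 1200 = 60 (15 per PHC); × 0.8 = 48 (12 per PHC). Both are below 89. Reaching 89 needs detection of 89/1200 = 7.4%, or 89/960 = 9.3% after attrition.
- Intervention, difference absolute (25%): 300 (75 per PHC); 240 after attrition.
- Intervention, difference relative (6%): 72; about 58 after attrition.

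**3. Power on these counts.** Design effect = 1 + (m − 1) × ICC, where m is cases per PHC; effective size = cases / design effect; power = Φ[(0.20 − 1.96 SE₀)/SE₁], with SE₀ pooled and SE₁ unpooled.

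Example, 60 v 300 at ICC 0.1: design effects 1 + 14 × 0.1 = 2.4 and 1 + 74 × 0.1 = 8.4; effective sizes 25.0 and 35.7; SE₀ and SE₁ both about 0.124; power = Φ(−0.34) = 36.6%.

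| ICC | 60 v 300 | 48 v 240 | 60 v 72 | 48 v 58 |
|---|---|---|---|---|
| 0 | 85.7% | 77.7% | 67.1% | 57.4% |
| 0.01 | 77.5% | 70.2% | 60.8% | 52.6% |
| 0.02 | 69.9% | 63.6% | 55.4% | 48.5% |
| 0.05 | 52.6% | 48.8% | 43.5% | 39.1% |
| 0.1 | 36.6% | 34.8% | 32.0% | 29.8% |

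Eight clusters in two arms leave 8 − 2 = 6 degrees of freedom. A t reference on 6 df gives less: for 60 v 300, 59% at ICC 0.01, 39% at 0.05 and 28% at 0.1; for 48 v 240, 52%, 36% and 26%.

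**4. Which part does the damage.** Suppose 89 cases per arm were obtained, 22.25 per PHC. At ICC 0.1 the design effect is 1 + 21.25 × 0.1 = 3.125, the effective size 28.5 and the power about 35%. Meeting the case target does not restore 80% at that ICC.

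**5. Ceiling with four PHCs.** As cases grow without limit, the effective size per arm tends to 4/ICC. At ICC 0.1 that is 40, and power is 46% (pooled variance) to 48% (unpooled), or 36% on 6 df. At ICC 0.02 it is 200, and power is 98.8%. The ceiling falls below 89 only when ICC exceeds 4/89 ≈ 0.045.

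**The case against.** The best defence is that 1200 comes from the detection calculation, detection is the primary outcome, and no enrolment figure depends on the 89. That stands: the error changes a power claim, not the size of the trial. Several further points limit what can be said.

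- **A reader might infer that no number of cases could rescue recovery with four PHCs per arm.** That holds only at higher ICCs. At ICC 0.1 the ceiling is about 46–48%; at 0.02 it is close to 99%.
- **A reader might take 26–37% as the plan's power for recovery.** The article gives ICC 0.1 for detection. Carrying it over to recovery is an assumption, so only a range is defensible.
- **A reader might infer that the shortfall below 89 control cases is decisive by itself.** It is not. If the 20% is absolute, the larger intervention arm compensates: 60 v 300 independent cases give 85.7%. Attrition lowers this to 77.7%, and clustering does most of the rest.
- **A reader might treat 60 as a ceiling.** It is what the 5% implies. Control health workers are also sensitised, supervised and asked to screen, so actual detection could be higher. It could also be lower for this purpose: the 5% is for depression, while follow-up counselling is for mild cases, and scores of 10 or more are referred.

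None of this supports the sentence as printed. The only cell in the table above 80% requires no clustering, no attrition and an absolute 20% all at once.

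**Conclusion.** The point holds. The 89 per arm is correct arithmetic for a different design, and the step from 89 patients to 1200 screened adults does not follow. On the plan's own detection and attrition figures, the stated 80% power for recovery is not delivered: at ICCs from 0.01 to 0.1, power by normal approximation is 78% down to 37% for 60 v 300, 70% down to 35% for 48 v 240, and 61% down to 32% for 60 v 72. With attrition applied, 80% is missed even at ICC zero.

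This rests on reading the 5% as a share of all enrolled adults, on equal numbers of cases per PHC, and on a recovery ICC that the article does not state. If the 5% includes cases that are referred and not counted for recovery, there are fewer cases than shown. The exact power is therefore uncertain, but its direction is not. The primary detection outcome is not touched by this point.

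**What to change.** In Sample size:

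1. Remove the closing sufficiency sentence as it applies to recovery.
2. State that 89 per arm is unadjusted for clustering and attrition.
3. Give the expected number of mild cases per arm. Say whether the 20% detection difference is absolute or relative, and what share of detected cases is assumed to be mild. The 60 and 300 above should not be copied in as mild-case counts without that share.
4. Replace 80% with the clustered power, or the expected confidence interval width, over a stated ICC range for recovery (for example 0.01 to 0.1), and note that detection is the primary outcome.

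The cost is wording and a less favourable stated figure. No extra participants, PHCs or changes to patient care are needed.
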